**Methods and analysis:**

We will conduct a stepped-wedge cluster RCT in 60 general practices within the RCGP Research and Surveillance Centre (RSC) network. Groups of 10 practices will be randomised into the active phase at 2-monthly intervals over 12 months. All practices will be activated for at least 2 months. The primary outcome is the primary care interval measured as days between the first recorded symptom of cancer (within the year prior to diagnosis) and the subsequent referral to secondary care. Other outcomes include referrals rates and rates of direct access cancer investigation.

Analysis of the clustered stepped-wedge design will model associations using a fixed effect for intervention condition of the cluster at each time step, a fixed effect for time and other covariates, and then include a random effect for practice and for patient to account for correlation between observations from the same centre and from the same participant.

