## Methods and analyses

### Outcomes and outcome definitions

#### Primary outcome: primary care interval for cancer diagnoses

The primary care interval is defined as the number of days between the first recorded symptoms of cancer (within the year prior to diagnosis) and subsequent referral for secondary cancer care.^22^ In line with published research and guidelines on diagnostic intervals, we will search the patient record for coded symptoms during the year prior to diagnosis for all patients with a cancer diagnosis: 1 year is a trade-off between misattributing unrelated symptoms occurring more than a year before and missing symptoms of relevance by restricting to a shorter period.^22 23^

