### Randomisation and blinding

The eligible practices will be ranked according to their list size from smallest to the largest by the RCGP RSC. These will then be stratified into 10 strata (by list size) such that each strata contains the same number of practices. This is based on the allocation of 10 practices per step. Practices will be randomised in blocks of 10 to the timing of activation of the E-SN toolkit and will crossover in these blocks to the activated phase every 2 months. Therefore, practices will contribute between 2 months and 12 months of E-SN toolkit-activated time (figure 1).

A statistician ([name], Nuffield Department of Primary Care Health Sciences, University of Oxford) who is independent to the intervention development and implementation will produce a stratified randomisation schedule so that within each strata, practices are randomly allocated to each of the six steps, with some replacement practices. The random sequence will be generated using R software. The allocation will be undertaken for all practices at the same time. Where replacement practices are required, these will be taken from the same strata where possible. If no replacement practices from the same strata are available a coin toss will determine whether the next highest or lowest strata will be used to provide replacement practices.

Given the practice change nature of the intervention, clinicians and practice managers will be aware when their practice has switched to the intervention period. Consulting patients providing outcome data will not be informed of the experimental nature of the E-SN toolkit activation and therefore will be blind to the stage of study occurring in the practice they attended. Study personnel involved in extracting outcome data will be blind to the allocated order of the delivery of the intervention across the practices. All data management of extracted data to calculate the outcome measures will be conducted blinded to the timing of switching to intervention. Similar methods have been used in other implementation SW-CRCTs.^26^

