### Sample size

Practice lists sizes within the RCGP RSC are approximately 10 000. In England, diagnosis rate of new cancer was 523/100 000 per year (2014/2015).^30^ Therefore, we could expect 53 new cancers per year per practice. Therefore, in each 2-month step, there would be 8–9 cancers per cluster.

The median primary care interval between first presentation and specialist referral^22 31^ is 5 days, IQR of 0–27.^32^ Some cancers present with clear red flag symptoms leading to immediate specialist referral. Presentations of vague symptoms such as weight loss are less likely to be immediately referred and may benefit from using the safety-netting template. This symptom is associated with several cancers such as prostate, colorectal, lung, gastro-oesophageal and pancreatic.^33^ The median primary care interval for lung cancer is 14 days (IQR 2–45).^32^ Using Stata V.14 to conduct the sample size calculations we showed that with the design in figure 1 and 60 practices we would be able to detect an effect size of 2 days with 80% power.

Currently, approximately 19% of cancers are diagnosed following an emergency presentation.^34^ With nine cancers per step per cluster we would be powered to detect a difference of 5%.

Under another scenario of considering primary care intervals towards the 90th centile of 60 days, with 60 practices, entering the stepped wedge design in six steps we would be able to detect a minimal difference of 13 days. However, if we consider that these patients with longer delays are in the 90th centile, then instead of expected cancers per cluster per step of 9—there would be around 1. This would allow us to detect a minimal difference of between 9 and 39 days dependent on the assumption of the distribution of the primary care delays.

Several scenarios are shown in table 3, all based on 60 practices, entering in six blocks, with a 12-month preintervention period. In summary, our main analysis will focus on all cancers, but we can conduct prespecified subgroup analyses restricting to cancers that typically have longer delays.

**Table 3 T3:** Scenarios for various assumptions used in the sample size calculations

Assumptions	All cancers (based on lung cancer)	All cancers	All cancers	All cancers	Restricting to only 90^th^ centile delays	Restricting to only 90th centile delays
Median (days)	14	14	60	60	60	60
Range (days)	0–60	0–100	0–365	0–100	14–100	14–365
N of cancers per step per cluster	9	9	9	9	1	1

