### Statistical analysis

In patients with a diagnosis of cancer, we will calculate the primary outcome of primary care interval (time between first recorded symptom and referral), proportion diagnosed after emergency presentation and the recorded diagnosis. Among consulting patients, we will calculate the rate of direct access cancer investigation and rates of referrals via 2 weeks wait, urgent and routine pathways, as well as the number of consultations during the primary care interval, and the template activation rate. A patient referred to: a 2-week wait pathway will be reviewed by a specialist within 2 weeks; an urgent pathway will be reviewed as a priority but the exact timing varies between specialty and healthcare setting; a routine pathway requires specialist review but on a non-urgent basis.

Regarding the analysis of the stepped-wedge design and the effect of correlation of observations within clusters, will model the association using a fixed effect for the intervention condition of the cluster at each time step, a fixed effect for time and other covariates (eg, changes in cancer guidelines), and then include a random effect for practice and a random effect for patient to account for correlation of the observations from the same centre and from the same participant.

Analyses will include all patients registered at participating practices. Practices that withdraw their agreement to participate will be included in analyses up to the point of withdrawal, unless they indicate that they wish to withdraw previously collected data from analysis.

Our primary analysis will be carried out on an intention to treat principle. Therefore, if any practice does not switch on the E-SN toolkit at the correct time for their cluster, we will carry out the analysis under the assumption that the E-SN toolkit was switched on at the correct time.

The primary care interval is defined from the presence of symptoms and referral in the primary care record. Symptoms of interest will include all symptoms included in the urgent referral guidelines including vague symptoms such as weight loss, tiredness and back pain.^35 36^ Missing data for these variables in the record will be interpreted as the absence of symptoms or referral, respectively. Extracted data from the primary care record will be limited to the study period plus the preceding year, so symptoms recorded prior to this will not be visible to the research team.

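### For outcomes recorded once per cancer, the stated patient random effect is redundant, and the absence of a practice-by-step effect can make the intervention standard error too small

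*Protocol article*

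**What the plan says.** The Statistical analysis section gives one sentence on modelling. It is introduced as covering the stepped-wedge design in general and is not tied to a particular outcome. The fixed part is "a fixed effect for the intervention condition of the cluster at each time step, a fixed effect for time and other covariates". The random part will "include a random effect for practice and a random effect for patient to account for correlation of the observations from the same centre"; repeated observations on one person are named as the second reason. The Abstract repeats the structure: "then include a random effect for practice and for patient to account for correlation". Neither place mentions a practice-by-step effect, a correlation that decays with time, or a robust variance.

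The primary outcome is "the number of days between the first recorded symptoms of cancer (within the year prior to diagnosis) and subsequent referral for secondary cancer care". Its population is stated as follows: "In patients with a diagnosis of cancer, we will calculate the primary outcome of primary care interval". The same section also lists outcomes of another kind: "Among consulting patients, we will calculate the rate of direct access cancer investigation", together with referral rates by route.

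The Sample size section describes its scenarios as "all based on 60 practices, entering in six blocks, with a 12-month preintervention period". Under Randomisation and blinding, "practices will contribute between 2 months and 12 months of E-SN toolkit-activated time".

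**The concern.** **Patient effect.** A patient random effect models correlation between repeated observations on one person. Apart from the occasional second cancer, a patient contributes one primary care interval. The same holds for emergency presentation, for consultations before referral, and for total time to diagnosis among cancer patients. For these outcomes the term has no repeated data to work on. It may cause a fitting failure or an arbitrary split of variance in the trial's main analysis.

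**Practice effect.** With a practice intercept as the only cluster term, two patients of the same practice are taken to be equally correlated whether they are diagnosed in the same 2-month step or almost two years apart. The intervention estimate draws on comparisons between periods within a practice. If staffing, coding habits or local referral routes change over time in a practice-specific way, that variation enters the estimate, but the model counts it as patient-level noise. The fixed effect for time removes only the change that all practices share. The error runs in the anti-conservative direction: confidence intervals too narrow, and too many false claims of an effect.

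**Working it through.** **1. Patient effect, linear model.** Write the interval of patient *j* in practice *i* as fixed part + practice effect (variance τ²) + patient effect (variance ω²) + residual (variance σ²). With one interval per patient:
- variance of an observation = τ² + (ω² + σ²)
- covariance of two patients in one practice = τ²

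Only the sum ω² + σ² appears. The likelihood is flat in the split, and the intervention estimate and its standard error do not depend on it. For one binary value per patient (emergency presentation), the observation carries no information on a patient variance apart from its mean, so that variance is not identified. In a Poisson-type model for the consultation count, the term would act only as overdispersion, not as within-patient correlation.

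**2. Inputs for the practice-by-step check.**
- From the Sample size section: 60 practices, six blocks of 10, a 12-month pre-period, and 8-9 cancers per cluster per step (9 used).
- From Randomisation and blinding: activated time of 2 to 12 months, so the first block is active from the first trial step.
- Assumed: the pre-period is divided into six 2-month periods (12 periods in all), with a separate fixed effect for each period; two-sided 5% test; SD = range/4 = 60/4 = 15 days for the 0-60 day scenario; ICC 0.01, 0.05 or 0.10.
- Assumed between-step correlation, relative to within-step: constant (ratio 1), ratio 0.8, ratio 0.5, or decay of 0.9 per step.

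**3. The plan's own figure.** The 2-day detectable difference cannot be rebuilt from stated inputs alone, because SD, ICC and alpha are absent. Under the assumptions above, with a practice intercept only, minimum detectable difference = (1.96 + 0.84) × SE. At ICC 0.05 the SE is 0.719 days, so 2.80 × 0.719 = 2.01 days. Over ICC 0.01 to 0.10 the result is 1.96 to 2.01 days, which agrees with the stated 2. The same SD rule gives about 3.3 days for the 0-100 day scenarios (Table 3: 5 and 4) and 12.2 for 0-365 (Table 3: 13), so it does not explain all of Table 3.

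**4. Planned model against the assumed truth.** Let V be the true covariance of a practice's 12 period means and W the covariance under a practice intercept only, with its variances set to their expected-likelihood values. X is the design matrix, and sums run over practices.
- Model variance: A⁻¹, where A = Σ X′W⁻¹X
- True variance of the same estimator: A⁻¹ (Σ X′W⁻¹VW⁻¹X) A⁻¹
- Type I error = 2 × [1 − Φ(1.96 × model SE / true SE)]

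Example, ICC 0.05 and ratio 0.5 (SD 15): model SE 0.716, true SE 0.782, quotient 0.916. Then 1.96 × 0.916 = 1.795 and type I error = 7.3%.

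| ICC | Constant | Ratio 0.8 | Ratio 0.5 | Decay 0.9 per step |
|---|---|---|---|---|
| 0.01 | 1.000 (5.0%) | 0.993 (5.2%) | 0.984 (5.4%) | 0.973 (5.7%) |
| 0.05 | 1.000 (5.0%) | 0.963 (5.9%) | 0.916 (7.3%) | 0.877 (8.6%) |
| 0.10 | 1.000 (5.0%) | 0.924 (7.0%) | 0.843 (9.9%) | 0.784 (12.4%) |

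Each cell shows model SE / true SE, with type I error in brackets.

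**5. Checks.** Simulation of the planned model (2,000 trials per setting) gave 4.6-5.2% with constant correlation, 5.5% at ICC 0.05 and ratio 0.8, 7.0% at ICC 0.05 and ratio 0.5, and 7.1% at ICC 0.10 and ratio 0.8. At ICC 0.01-0.02 and ratio 0.8 it showed no inflation (4.3-5.1%). The decay case was calculated but not simulated. The way the pre-period is divided matters little: at ICC 0.05 and ratio 0.5, type I error is 6.9% with a single pre-period of 9 cancers and 6.8% with no pre-period.

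**The case against.** The strongest reply has four parts.

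- **The sentence is general.** It covers the stepped-wedge analyses as a whole and follows a list that includes referrals and investigations among consulting patients, who can appear in several periods. For those outcomes a patient effect is legitimate. Total time to diagnosis is also measured in all patients with an activated template, so it is not confined to cancer patients. This stands. The fault is that the sentence assigns the term to every outcome without distinction.
- **The patient effect does no inferential harm in the linear model.** A reader might infer that it is what shrinks the standard error. Step 1 of the working shows that it does not; only the missing practice-by-step term can do that.
- **The inflation is conditional.** A reader might infer that the standard error is certainly too small. The article gives neither an ICC nor a between-step correlation. With constant correlation the error is 5.0%, and at ICC 0.01 the excess is trivial.
- **The pandemic does not settle it.** The section on COVID-19 describes large changes in consulting and referral, but it also says that the start was delayed to limit them. Disruption common to all practices is absorbed by the time effect. Only practice-specific disruption would matter, and the article gives no evidence of its size.

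A separate analysis plan could add a practice-by-step term or a robust variance without contradicting the article. That softens the point but does not remove it, because the article states its random effects explicitly, twice, and the structure given does not suit the primary outcome.

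**Conclusion.** The point holds in two separate parts. For outcomes recorded once per cancer, the patient effect is redundant with the residual, apart from rare second cancers. It is a nuisance for fitting in the linear model, and for a binary outcome its variance is not identified. Independently, the practice-only intercept rests on equal correlation within and between steps over 24 months. If that fails, the model standard error is too small by about 1-3% at ICC 0.01, 4-12% at ICC 0.05 and 8-22% at ICC 0.10 across the three patterns examined. The corresponding type I errors are 5.2-5.7%, 5.9-8.6% and 7.0-12.4%. All of these rest on assumed ICCs and between-step correlations, and the documents do not show which setting applies. The point should be fixed before analysis, but it does not invalidate the design.

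**What to change.** State the random effects by type of outcome.
- **Once per cancer** (primary care interval, emergency presentation, consultations before referral, total time to diagnosis in cancer patients): drop the patient effect and fit random effects for practice and for practice-by-step (nested exchangeable), with a decaying-correlation structure as a sensitivity analysis.
- **Repeatable by a patient** (referrals, direct access investigations): keep the patient effect.

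This takes a sentence or two in the analysis section and no new data. The price is slightly wider intervals and a small loss of the stated power. With SD 15 days, the detectable difference under a model with the practice-by-step effect is 1.96 days at ICC 0.01 and ratio 0.8, 2.09 at ICC 0.05 and ratio 0.8, 2.19 at ICC 0.05 and ratio 0.5, and 2.38 at ICC 0.10 and ratio 0.5. Power at 2 days is then 82%, 76%, 73% and 65%. The last is the least favourable of these settings. If the practice-by-step variance proves to be near zero, the change costs almost nothing.

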**Figure 1 F1:**
[figure not shown]
Stepped-wedge design with 12 months prerandomisation period. Pale blue cells represent inactive E-SN period, and purple cells represent active E-SN period. E-SN, electronic safety-netting.

This paper describes the protocol dated 7 October 2019 (V.1.5). Core trial information is given in table 1.

**Table 1 T1:** WHO trial registration data set

Data category	Information
Primary Registry and Trial Identifying No	ISRCTN: ISRCTN15913081
Date of Registration in Primary Registry	08/11/2019
Secondary Identifying Numbers	N/A
Source(s) of Monetary or Material Support	Cancer Research UK; Grant Codes: C48270/A27880
Primary Sponsor	University of Oxford
**Secondary Sponsor(s)**	None
Contact for Public Queries	[contact]
Contact for Scientific Queries	[contact]
Public Title	Testing an electronic safety netting system to help GPs follow-up patients with worrying symptoms
Scientific Title	CASNET2: Evaluation of an e-safety netting cancer template in primary care: a pragmatic stepped-wedge RCT
Countries of Recruitment	UK
Health Condition(s) or Problem(s) Studied	E-safety netting (E-SN) toolkit.
Intervention(s)	The researchers will recruit 60 general practices who are not currently using the E-SN toolkit, and randomise them in clusters (groups) of 10. Each cluster will have the E-SN toolkit turned on at a different time during the 12 months of the study. Once the E-SN toolkit is turned on, the GPs in the practice will be able to use it when caring for any patient they think would benefit from it, although it is expected that it will be of most use when treating patients with symptoms that might indicate cancer. The researchers will collect data from the electronic patient record system from the 12 months of the study and the 24 months before the start of the study to understand whether the introduction of the E-SN toolkit makes any difference to the diagnosis of cancer, and in particular to how quickly patients are diagnosed. The researchers will only extract records from patients who are over 18, and who have not opted out of the research.

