### Data extraction

Data extractions from all participating practices will correspond to two major time points: at the start of the introduction to the stepped wedge implementation of the E-SN toolkit, and at the end of the stepped wedge period (12 months later). At these two time points, consultation data from the participating practices will be obtained for the previous 24 months. Data from the previous 24 months are required to identify cancers detected in 12 months prior to start, plus the first recorded symptom of cancer during the primary care interval, allowing for this interval to cover up to a year prior to diagnosis.

Records from all patients who are adults aged 18 years and above, registered at participating practices and who have not opted out of sharing data for research purposes will be extracted. Pseudonymised patient information will include: demographic information of age, sex, dates of clinical consultations; coded consultation data for symptoms, diagnoses, tests ordered and referrals made within the consultation records. Where a definitive diagnosis has been made (for cancer and non-cancer conditions), the clinical features recorded in the year prior to diagnosis will be captured. These actions will be achieved by extraction of the EHR rather than by hand searching notes.

Practices will be asked to search for open diary entries every week during the intervention period, and to download and save these to an Excel spreadsheet (locally). The central study research team will use these spreadsheets to track which diary entries are closed during the course of the intervention.

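### The extraction window gives a cancer code only 12 to 36 months of earlier record, so an older cancer coded again can pass as new, most clearly in the emergency-presentation outcome

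*Protocol article*

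**What the plan says.** **Window.** Data extraction takes records twice, at the start and at the end of the 12-month wedge: "At these two time points, consultation data from the participating practices will be obtained for the previous 24 months". It gives the reason: "Data from the previous 24 months are required to identify cancers detected in 12 months prior to start, plus the first recorded symptom of cancer", with that symptom search reaching back up to a year before diagnosis. Table 1 agrees on the span: "the 12 months of the study and the 24 months before the start of the study". Statistical analysis puts it as "Extracted data from the primary care record will be limited to the study period plus the preceding year", and the only consequence it draws is that earlier symptoms will not be seen.

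**Cases.** For the primary outcome, "we will search the patient record for coded symptoms during the year prior to diagnosis for all patients with a cancer diagnosis". All adults who have not opted out are eligible, with no exclusion for earlier cancer. The Sample size section counts new disease: "we could expect 53 new cancers per year per practice".

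**Emergency presentation (table 2).** A cancer counts if its diagnosis precedes referral. If the route is uncertain, RCGP RSC will contact the practice, and algorithms are to be developed. Under Statistical analysis, an absent referral code is read as no referral.

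**The concern.** The outcomes and the expected number of cases are about new cancers. To know that a cancer is new, one must see that it was not coded earlier. The window allows for 12 months of baseline cancers plus 12 months of symptoms, and nothing for that purpose. A cancer diagnosed several years ago and coded again, for example after a clinic letter, at a review or on transfer of the record, may have no earlier code in the extract and would look new.

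This matters now because it concerns which data are taken. A later analysis plan can define a new cancer in any way it likes, but it cannot apply that definition to codes that were not extracted. The Patient confidentiality section also rules out linkage to other sources by the research staff.

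**Working it through.** **1. The plan's own figures.**
- Cases: 10,000 × 523/100,000 = 52.3 per practice-year, or 8.7 per 2-month step. The plan states 53 and 8–9, so it agrees, and the rate is one of new cancer.
- Detectable differences: I used the Hussey–Hughes stepped-wedge variance with 60 practices, six sequences of 10, six baseline and six wedge periods of 2 months, and 9 cancers per cell. Two-sided α of 0.05 and an intracluster correlation of 0 to 0.20 are my assumptions. From 19%, the detectable difference in emergency presentation is 4.8–5.3 points (stated: 5). With SD = 60/4 = 15 days (assumed), it is 1.8–2.0 days for the primary outcome (stated: 2).

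**2. Look-back.** Extraction starts at month −24, so a code entered at month *t* has *t* + 24 months of earlier record.

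| Date of code | Earlier record |
|---|---|
| Month −12 (start of baseline year) | 12 months |
| Month 0 (start of wedge) | 24 months |
| Month +12 (end of wedge) | 36 months |

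A cancer already coded within that span can be recognised as old. One last coded before it cannot.

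**3. What a re-coded cancer does to each outcome.**
- *Emergency presentation:* with no referral in the window, the case meets the definition. Practice contact is triggered by doubt about route, not about whether the cancer is new.
- *Primary outcome:* the case has an interval only if a listed symptom was coded in the prior year and a referral followed. Otherwise it drops out. The symptom condition is not strict, since tiredness and back pain are on the list.

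**4. Illustrative size.** Let *c* be the share of analysed cases that are old cancers. The documents do not give it, so the values below are assumed, with no toolkit effect in these cases.
- Diluted effect = true effect × (1 − *c*).
- Power = Φ[(1.96 + 0.84)(1 − *c*) − 1.96], holding the planned standard error.
- Apparent emergency proportion = 0.19(1 − *c*) + *c·q*, where *q* is the share of old cancers without a referral.

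| *c* | 2-day effect becomes | 5-point effect becomes | Power (planned 80%) | 19% becomes, *q* = 0 | 19% becomes, *q* = 1 |
|---|---|---|---|---|---|
| 2% | 1.96 | 4.9 | 78% | 18.6% | 20.6% |
| 5% | 1.90 | 4.75 | 76% | 18.1% | 23.1% |
| 10% | 1.80 | 4.5 | 71% | 17.1% | 27.1% |
| 20% | 1.60 | 4.0 | 61% | 15.2% | 35.2% |

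At *c* = 6% and *q* = 1: 0.94 × 19% + 6% = 23.9%, a shift in level as large as the 5-point detectable difference. That needs 52.3 × 0.06/0.94 ≈ 3.3 re-coded cancers per practice-year.

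The power column takes the old cancers as part of the planned number. If they come on top of it, the standard error shrinks by about √(1 − *c*) and the loss is smaller: Φ[2.80 × √(1 − *c*) − 1.96] gives about 79% at 2% and 71% at 20%.

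**5. Comparison between conditions.** Look-back depends on calendar date alone and lengthens equally in every practice. The model has a fixed effect for time, which should absorb most of any resulting trend.

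**The case against.** The strongest reply is that this is a matter of case definition. An article leaves code lists and first-versus-repeat rules to the full protocol or analysis plan, and the text speaks of new cancers throughout. That stands as far as the definition goes: its absence here is not the point. The extraction window is stated here, however, and it limits how any definition can be applied.

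A second reply is that RCGP RSC holds the practice record and could check earlier codes before release. It may be able to. The article does not say that it will, and the fix asks for exactly this.

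A reader might also infer more than the documents support:
- *That only one year of record precedes any code, or that no old cancer can be recognised.* Taken alone, the sentence in Statistical analysis could mean extraction from month −12. Table 1 and Data extraction give 24 months before the start, and old cancers coded within the look-back are visible.
- *That old cancers generally enter the primary outcome.* They need both a prior-year symptom and a later referral. A recurrence with new symptoms and a new referral is also a pathway that the toolkit could affect.
- *That the shorter look-back in the all-inactive baseline year biases the comparison.* The fixed time effect should absorb most of this, unless activation itself changes re-coding.
- *That a large share of cases is false.* Assuming, say, 200–300 patients with past cancer per practice and 2–10% re-coded yearly gives 4–30 cases beside 53, or 7–36%. Neither input is in the documents, and the sum counts every re-coded case as analysed.

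**Conclusion.** The point holds as a limit of the extracted data. A cancer last coded before the 12- to 36-month look-back and coded again in the window cannot be distinguished from a new one. That old cancers will be counted is a risk, not something the document states.

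The risk is clearest for emergency presentation, a secondary outcome, where the table 2 safeguards check route rather than newness. For the primary outcome it is conditional and amounts mainly to dilution and noise. The size is unknown: under the assumed shares it runs from negligible (1.96 instead of 2 days at 2%) to material (1.60 days at 20%). The conclusion that harm is not differential rests on the fixed time effect and on re-coding being unaffected by activation. The change is worth making because it is cheap before extraction and would need a new extraction afterwards.

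**What to change.** - Have RCGP RSC derive one item before pseudonymised release: the date of the first-ever cancer code by site, searched over the whole record.
- Restrict the main analysis to cancers whose first-ever code for that site falls in the analysis window.
- Add two sensitivity analyses: one that keeps later codes at the same site (possible second primaries or recurrences), and one that excludes patients with any earlier cancer.
- Amend Data extraction and Statistical analysis so that the one-year limit applies to symptoms only.

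**Cost.** One more variable in the query, a small change of wording, and no work for practices. The item must be justified against the commitment to minimise data under Patient confidentiality; a single derived date keeps it narrow. Some genuine second primaries at the same site will be lost from the main analysis, which the first sensitivity analysis shows. The delayed start described in the COVID-19 section may give time to do this before extraction.
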